### Randomization

Eligible subjects enrolled in the study will be randomized (1:1) at baseline to receive either MMF_PK_ or MMF_BSA_. Randomization will be stratified by LN class (class 3 or 3/5 ***vs.*** class 4 or 4/5) as per the ISN/RPS and extrarenal manifestations of cSLE (extrarenal SLEDAI score<10 ***vs.*** ≥ 10). Race (white or non-white) and belimumab treatment (yes/no), as well as other important factors which have a known association with long-term outcomes of LN will be considered as potential confounders during the analyses. We will use variable block sizes to ensure balance and to minimize risk for unmasking. Thus, we will be using block sizes of 4 and 2 in random order.

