### Outcome measures and safety and efficacy endpoints

The primary efficacy outcome of the study is the improvement of proliferative LN as measured by the presence of at least PRR at the end of Part 1 of the study (week 26). The major secondary outcome is the achievement of CRR at the end of Part 1 of the study. Other secondary outcomes are the achievement of CRR at the end of Part 2 of the study (week 53) and frequency of adverse events defined as grade 3 or higher during all parts of the study using the National Cancer Institute Common Terminology Criteria for Adverse Events.

Exploratory outcomes include: change in Renal Activity Index for Lupus (RAIL) score (baseline visit to week 53) [23,24], rate of LN flares, time to PRR and CRR during the study (baseline visit to week 53), mean time-adjusted score of the Systemic Lupus Erythematosus Disease Activity Index (SLEDAI) [25], considering extra-renal domain items during the study (baseline visit to week 53), cumulative dose of oral corticosteroids (CS; in prednisone-equivalents) and cumulative exposure to intravenous CS during the study, frequency of patients fulfilling discontinuation criteria during the study, change in health-related quality of life as measured by the Pediatric Quality of Life Inventory (PedsQL) Generic Core Scale [26], during the study, percentage of patients with intake of ≥ 80% of prescribed MMF doses as per blister-pack count during the study, and presence of MPA-levels<0.1 mg/L from random testing or in-clinic testing during the study. The MPA primary and secondary outcome evaluations will be performed by independent blinded evaluators at the CCC, according to validated criteria. Outcome definitions are provided in Table 2.

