### Statistical analysis

The primary outcome, superiority of MMF_PK_ over MMF_BSA_ for the percentage of subjects with clinical remission of LN (PRR, CRR) at the end of Part 1, will be tested using the analytical approach for the binomial outcome, such as Chi-square test, Fisher’s exact test, or a Bayesian approach with non-informative Beta prior for the binary probability parameter.

The choice of approach will be determined by the distribution of the data. Subjects who discontinue the treatment due to any reason will be considered as being non-responders. All secondary and exploratory efficacy outcomes will be analyzed by treatment group. For the binary secondary or exploratory outcomes, the analytical approach for the binary outcome, as used for the primary analysis, will be performed.

For the continuous exploratory endpoints, including change from baseline in PROMIS scores or RAIL scores, a mixed-effect model with repeated measures will be applied. The Kaplan-Meier plots will be generated for the exploratory endpoints of time to CRR and time to PRR. Since no measures are collected from the discontinued subject, the analyses will take an Inverse Propensity Weighting (IPW) approach where the propensity for subjects to be discontinued from each arm are estimated using logistic regression modeling or the covariate balance propensity score method.

The IPW approach will create pseudo subject samples that represent the original randomized subject cohort at the beginning of the study, and therefore addresses the missing data issue due to subject discontinuation.

Descriptive/summary statistics for all endpoints, with 95% confidence interval for treatment difference, will be provided. Baseline demographic characteristics, primary and major secondary outcomes will also be summarized overall and by age (<12 years ***vs.*** ≥12 years), gender and race (white ***vs.*** non-white). Safety analysis will be performed on all subjects who received at least one dose of study drug. Safety data will be subject to clinical review and summarized by appropriate descriptive statistics.

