**Figure 2: F2:**
[figure not shown]
The PLUMM Study design. Note: R-randomization; MMF_BSA_-treatment arm of MMF dosed at 600 mg/m^2^ body surface area about 12 hours apart; MMF_PK_-treatment arm of MMF dosed twice daily to achieve an area under the concentration-time curve (AUC_0–12h_) of MPA ≥ 60–70 mg*h/L, CRR-complete renal response; PRR-partial renal response; NR-non-responder; CYC-cyclophosphamide.

**Table 1: T1:** Key eligibility criteria.

Key inclusion criteria	Key exclusion criteria
1. Age 8-<18 years at the time of enrollment	1. Presence of features (from SLE or other chronic disease) that a-priori suggests that the subject benefits from other therapies than that suggested or allowable by the study protocol.
2. New diagnosis with proliferative LN as per the ISN/RPS classification criteria [21], based on kidney biopsy done within 60 days of enrollment. For study inclusion, the kidney biopsy needs to be newly interpreted as one of the following classes: class 3, class 3/5, class 4, or class 4/5	2. History of significant kidney disease prior to the diagnosis of SLE
3. Diagnosis with cSLE [47,48], per the classification criteria of the ACR [49]/EULAR [50] (i.e., SLE with diagnosis prior to or at age 18 years)	3. Estimated GFR <40 mL/min/1.73 m^2^ using the modified Schwartz equation [55].
4. Tolerates MMF as per the treating physician	4. Need for renal replacement therapy at the time of enrollment
5. SLEDAI-R [25,51–54], score>0	5. CYC within 12 weeks of enrollment
	6. Anti-CD20 monoclonal antibody treatment within 6 months, except if CD19/20+ counts are normal by flow cytometry analysis)
	7. Specific blood dyscrasias

**Note:** LN-lupus nephritis; ISN/RPS-International Society of Nephrology/Renal Pathology Society; cSLE-childhood-onset systemic lupus erythematosus; ACR-American College of Rheumatology; EULAR-European League Against Rheumatism; MMF-mycophenolate mofetil; SLEDAI-R-renal domain score of Systemic Lupus Erythematosus Disease Activity Index; GFR-glomerular filtration rate; CYC-cyclophosphamide.

**Table 2: T2:** Definition of key efficacy measures.

Outcome measure	Definition	References
Partial renal remission	PRR is defined as relevant improvement of 2 LN-RV* with the remaining LN-RV being at least stable.	[22,34]
Complete renal remission	CRR is the presence of all 3 LN-RVs within normal range.	[22,34]

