Lupus nephritis flare	A LN flare is the reproducible+ presence of 1 or more of the following (a-d) that is at least partially due to renal inflammation from LN per the treating physician. a. Newly abnormal GFR plus increase in hematuria by at least 2 categories (normal: 0 to 5 RBC/HPF (normal), 6 to 10 RBC/HPF, 11 to 25 RBC/HPF, 26 to 50 RBC/HPF, >50 RBC/HPF) OR new gross hematuria (>50 RBC/HPF). b. Abnormal GFR that decreased by >10% plus increase in hematuria by at least 2 categories (normal: 0 to 5 RBC/HPF (normal), 6 to 10 RBC/HPF, 11 to 25 RBC/HPF, 26 to 50 RBC/HPF, >50 RBC/HPF) OR new gross hematuria (>50 RBC/HPF). c. Persistent increase of UPCR to >0.5, after CRR d. Persistent doubling of UPCR with values >1.0, after PRR	[22,34]

**Note:** PRR-partial renal response; LN-RV-lupus nephritis core response variables; CRR-complete renal response; GFR-glomerular filtration rate; RBC/HPF-red blood cell per high-power field; UPCR-urine protein to creatinine ratio.

* LN-RVs are the upper limit of normal (ULN) or lower limit of normal (LLN) of the following:

Urine protein to creatinine ratio (ULN: 0.2), estimated GFR (LLN: 95 ml/min/1.73m^2^) and glomerular hematuria (ULN:0)

+ Reproducibility means presence on >2 subsequent time points >1 week apart.

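### PRR and CRR are built from UPCR, eGFR and hematuria, but the tests named for them use no covariates, so chance imbalance in baseline renal severity stays in the estimate and some precision is probably lost

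*Protocol article*

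**What the plan says.** All references are to the protocol article.

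- **Endpoints.** The primary outcome is at least PRR at week 26; CRR at week 26 is the major secondary outcome. Table 2 gives the definitions: "PRR is defined as relevant improvement of 2 LN-RV* with the remaining LN-RV being at least stable" and "CRR is the presence of all 3 LN-RVs within normal range". Its footnote lists the three response variables as UPCR, estimated GFR and glomerular hematuria, with normal limits of 0.2, 95 mL/min/1.73 m² and 0.
- **Tests.** Statistical analysis names, as examples for the primary outcome, a chi-square test, Fisher's exact test, or "a Bayesian approach with non-informative Beta prior for the binary probability parameter". Binary secondary and exploratory outcomes follow the same approach.
- **Covariates.** Randomization stratifies by LN class and by extrarenal SLEDAI (below 10, or 10 and above). It then says that "Race (white or non-white) and belimumab treatment (yes/no), as well as other important factors which have a known association with long-term outcomes" of LN are to be considered as potential confounders in the analyses. The other factors are not named.
- **Entry.** Table 1 excludes eGFR below 40 and asks only for a renal SLEDAI score above 0. It also requires a new diagnosis "based on kidney biopsy done within 60 days of enrollment" and a subject who "Tolerates MMF as per the treating physician".

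**The concern.** The article says that confounders will be handled, but none of the tests it names for PRR and CRR has a place for a covariate. Where it does intend modelling, for the continuous endpoints and for discontinuation, it says so.

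The variables most closely tied to response are also missing from the named list. CRR is a fixed cut on UPCR, eGFR and hematuria, so someone entering at eGFR 45 starts much further from it than someone entering at 100. PRR needs improvement in two of the three variables, so a subject with only one abnormal variable at entry may be able to respond only by way of CRR. Neither stratification factor is one of these three variables.

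With about 45 evaluable subjects per arm, the arms can differ in starting renal severity by chance. An unadjusted comparison carries that difference into the estimate. If baseline severity predicts response, it also forgoes precision from data that must be recorded anyway to score improvement.

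**Working it through.** **Inputs from the article (Sample size and power estimation).** 45 per arm; two-sided 5% chi-square test; PRR 55% vs 83%, stated power 80%; CRR 14% vs 43%, stated power 81%.

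**Assumption.** The article does not say how strongly baseline renal severity predicts response. The range taken is a log-odds of 0 to 1.5 per SD of a combined score, that is odds ratios of 1.0 to 4.5 (exp(1.5) = 4.48).

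**1. The plan's own power.** Power = Φ[(d − 1.96·SE₀)/SE₁], with SE₀ = √(2p̄(1−p̄)/n) and SE₁ = √((p₁(1−p₁)+p₂(1−p₂))/n).

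- PRR: d = 0.28, p̄ = 0.69, SE₀ = √(0.4278/45) = 0.0975, SE₁ = √(0.3886/45) = 0.0929. Power = Φ(0.957) = 83.1%. Exact enumeration of the Pearson test gives 84.4%.
- CRR: d = 0.29, p̄ = 0.285, SE₀ = 0.0952, SE₁ = 0.0901. Power = Φ(1.148) = 87.5%.
- With a continuity correction, n is replaced by (nd−1)²/(nd²). For PRR this is 11.6²/3.528 = 38.1, power 76.3%. For CRR it is 12.05²/3.784 = 38.4, power 81.6%.

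The stated 81% for CRR reproduces only with the correction. The stated 80% for PRR is about 3 points below the uncorrected test that the article names. The unadjusted design is therefore not short of power at its own rates.

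**2. Chance imbalance.** The SD of the between-arm difference in a standardised baseline score is √(2/45) = 0.211. P(|difference| > 0.2 SD) = 2[1 − Φ(0.2/0.211)] = 2[1 − Φ(0.949)] ≈ 34%, about 17% in each direction.

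**3. Simulation.** 20,000 trials per scenario, 45 per arm, the plan's marginal rates held fixed, three independent normal baseline covariates, no stratification and no dropout. The last two columns cover trials in which MMF_PK starts worse by more than 0.2 SD.

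| Odds ratio per SD (AUC) | Unadjusted PRR power | Logistic LR, 3 covariates | Adjusted risk difference, HC3 | Unadjusted power if MMF_PK starts worse | Shift in PRR difference |
|---|---|---|---|---|---|
| 1.0 (0.50) | 84% | 83.9% | 81.0% | 84% | 0 |
| 1.65 (0.63) | 84% | 85.4% | 82.5% | 76% | −3 points |
| 2.1 (0.69) | 84% | 86.9% | 84.2% | 72% | −4 points |
| 2.7 (0.74) | 84% | 88.9% | 86.8% | 69% | −5 points |
| 4.5 (0.81) | 84% | 92.8% | 90.2% | 64% | −7 points |

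For CRR, unadjusted power is about 89%, and the likelihood-ratio (LR) test gives 88.2, 89.5, 90.7, 92.9 and 95.3% over the same rows.

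**4. Type I error (69% in both arms).** The unadjusted test runs at 5.1–5.5%. The LR test with three covariates runs at 5.6–6.0%, so part of its apparent gain is inflation.

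**5. Gain with a re-randomisation p-value.** With two or three covariates at 45 per arm, PRR power rises by about 1–5 points at odds ratios of 2–3 per SD. At 1.5 or below it is flat or falls by about 1–3 points.

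**6. Model size.** The smaller outcome class is 90 × 0.31 ≈ 28 for PRR and 90 × 0.285 ≈ 26 for CRR. UPCR, eGFR, one ordinal hematuria term and arm make 4 parameters, or 28/4 = 7 and 26/4 = 6.5 subjects each. Entering Table 2's five hematuria bands as 4 terms and adding prior treatment time makes 8 parameters, or 28/8 = 3.5 and 26/8 ≈ 3.3. A model of about that size (7 covariate terms) lost power under re-randomisation at odds ratios of 2 or below.

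**The case against.** The strongest reply is that this is a condensed article. Covariate lists normally sit in an analysis plan that is not shown, the tests are introduced as examples, and the open wording on other important factors could take in the renal variables. That is why the point is not that a list is missing. What stands against the text is that it fixes on covariate-free methods for PRR and CRR, and an unnamed set of factors to be considered does not pre-specify an adjusted comparison. The contingent correction for corticosteroid dose in the Discussion concerns dosing during the study, not baseline.

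Four stronger readings are tempting, and the documents do not support them.

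- *Baseline is ignored.* PRR is scored as improvement, so baseline values already enter each subject's primary outcome, and LN class is a stratum. Scoring change does not remove dependence on the starting value, but the word ignored would be wrong.
- *The unadjusted test is biased or invalid.* It is neither. Its type I error is about 5%, and chance imbalance is already counted in that rate. The issue is precision, and accuracy given the imbalance that actually occurs.
- *Subjects may have had up to 60 days of treatment before entry, so week 26 could mean 34.6 weeks of therapy.* The 60 days is the window from biopsy to enrolment. The tolerance criterion implies some earlier MMF, but the length of prior MMF or steroid treatment is not stated.
- *Adjustment always gains power.* It does not. With weak covariates or too many terms it costs power, as the HC3 column and steps 5 and 6 show.

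**Conclusion.** The point holds as a recommended improvement to a valid analysis. PRR and CRR are functions of three variables whose baseline values must be recorded, while the named tests use none of them as covariates and the confounder sentence has no counterpart in those tests. Imbalance above 0.2 SD is expected in about one trial in three, and when it goes against MMF_PK the unadjusted power falls from 84% to about 64–76% over odds ratios of 1.65 to 4.5 per SD.

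Averaged over all trials, the gain from a small adjusted analysis is modest: about 1–5 points of PRR power at odds ratios of 2–3 per SD, and nil or a loss of about 1–3 points at 1.5 or below. The 34% follows from the sample size alone. The power figures rest on an assumed prognostic strength that the article does not give, and on simulations without stratification or dropout.

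**What to change.** Before unblinding, make the primary PRR comparison, and the CRR comparison in the same form, a small pre-specified adjusted analysis:

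- Covariates: log baseline UPCR and baseline eGFR, with baseline hematuria as one ordinal term at most.
- Estimate: a risk difference standardised over the trial population, with 95% CI.
- P-value: a re-randomisation test that repeats the actual stratified, blocked allocation, because the plain likelihood-ratio test is mildly inflated.
- Supportive: the simple chi-square test.
- Wording: in the Randomization section, say which of the confounders named there enter which analysis.

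The cost is text and some programming. No new data are needed, since scoring improvement already requires the baseline values. The drawbacks are a result that is slightly harder to present, and a loss of about 1–3 points of power if baseline severity turns out to predict response only weakly. That is the reason to keep the model small.

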### Blinding

Subjects and research personnel at the CCC and sites will remain blinded to the study intervention (MMF_PK_ or MMF_BSA_) until the end of the study. The following team members will remain unblinded: research pharmacist, unblinded study physicians, and the PK analysis team. During the study, masking will be maintained by using placebo capsules which have the same appearance as MMF. Genentech will supply MMF to the central pharmacy at Cincinnati Children’s Hospital Medical Center (CCHMC) Investigational Drug Service (IDS).

MMF tablets (500 mg/tab) and/or MMF capsules (250 mg/cap) and/or identical placebo capsules will be used to ensure double-blinding of the study treatment. Over-encapsulated MMF 250 mg and placebo capsules will be prepared by the IDS. Blister packs containing combinations of MMF 500 mg tablets, over-encapsulated MMF 250 mg, and/or placebo capsules are produced by the IDS to reflect the desired MMF dosage, based on the treatment arm. Each subject is instructed to take medication in the morning and evening from the appropriately labelled blister card containing 10 medication blisters. The appearance of study medication is changed after every study visit and study month, regardless of the treatment arm. After the final data lock, the site investigators will be informed of the treatment allocation.

### Investigational and reference therapy

MMF in tablet and/or capsule form will be taken twice daily by mouth, approximately 12 hours apart. The investigational therapy will be individualized using MMF_PK_ or MMF_BSA_. Based on PK assessment (as detailed in the next section), MMF dosage of the MMF_PK_ arm will be adjusted in 250 mg increments to achieve a target MPA-AUC_0–12_>60–70 mg*h/L. For the MMF_BSA_ arm, the amount of MMF prescribed will be around 600 mg/m^2^ BSA per dose, up to the recommended maximum of 3 grams per day. The dosage of MMF will be kept at the level prescribed on day 1 unless the patient’s weight changes. Necessary dose adjustments will be assessed whenever there is a weight change that exceeds 10 lbs. (or 4.5 kg) since the last dose. We expect trough levels of MPA to be>1–3.5 mg/L in both treatment arms.

### Pharmacokinetic assessment and Bayesian estimation

The study team developed a novel assay to measure MPA levels utilizing Volumetric Absorptive Microsampling (VAMS) devices from Mitra^®^ [27,28]. This will be used to measure MPA levels randomly or serially to assess MPA exposure and adherence to MMF. Capillary blood will be collected just prior to the next MMF intake (trough) and 20 minutes, 1 hour, and 3 hours after dose intake, which will then be sent to CCHMC for liquid chromatography tandem mass spectrometry (LC-MS/MS) drug assay and PK analysis. This method of PK assessment offers the convenient option of performing blood sampling for random MPA level measurement in the subject’s home setting.

The PLUMM study will use pharmacokinetic assessment at the following 5 patient visits during the study to adjust the dose of the MMF_PK_ arm subjects: baseline visit, week 3, week 10, week 26, and week 32. Dosing for this arm will be based on individual abbreviated AUC_0–12h_ estimates. These AUC_0–12h_ estimates will be generated with a well-established PK model-based Bayesian approach using MPA concentration results equivalent to plasma concentrations derived from capillary whole blood concentration results.

Two prospective studies were conducted at CCHMC and the University of Cincinnati ([name], PI; CCHMC IRB: 2022–0416) in preparation for the PLUMM study. These studies were used to validate the methodology of the PLUMM study using the VAMS device for PK-profiling and to ensure the study team can reliably convert capillary whole blood concentrations (as obtained with the Mitra VAMS device) to plasma concentrations. Individual PK parameters and dose to achieve the target AUC_0–12h_ will be estimated with Bayesian estimation using clinical precision dosing software MwPharm++ (Mediware, Prague, Czech Republic). The Bayesian estimation method and the sparse sampling strategy (at 0 h, 20 min, 1 h, and 3 h) for MPA have been developed and validated in various patient populations including pediatric lupus patients by [name] and colleagues at the Limoges University Hospital Laboratory of Pharmacology [29–32].

### Standardized steroid regimen

Corticosteroids (CS), mainly oral prednisone, are an integral part of treatment for patients with LN, but there is large variability of CS dosing among treating physicians [33]. Since CS have a strong anti-inflammatory effect that could influence the comparison of the two treatment arms and thereby affect the primary outcome of the study, site investigators are strongly encouraged to use the dose recommendations from the CCC which reflect a standardized steroid regimen as previously published by Chalhoub et al. [34].

Establishing a CS dosing algorithm was necessary to control the use of CS during the PLUMM study. Planning for the CS dosing was initiated with a retrospective chart review to document current use of CS at 15 sites. The chart review enabled the research team to build patient profiles to support consensus formation science using the Delphi methodology. The dosing parameters were developed based on the consensus ratings of 103 reviewing pediatric nephrologists and rheumatologists who rated 5056 patient profiles that outlined the disease course of LN patients. After the initial review, validation of the steroid dosing regimen was conducted with 60 raters on 1838 patient profiles. The resulting Standardized Steroid Regimen (SSR) has been published by Chalhoub et al. [34]. For the PLUMM study, the CCC will provide steroid dose recommendations based on data points from sites, using a calculator developed by one of the authors (BH).

### Phone application and other adherence tools

To alert subjects to random MPA testing and to remind of twice daily medication intake, the PLUMM phone application was developed which will be loaded onto the subjects’ device or parents’/caretaker’s device. We expect communication to occur primarily with the parent/caretaker. Random MPA measurements between study visits will be obtained if with suspected non-adherence or failure to log medication intake. An MPA level of<0.1 mg/L will be considered to reflect non-adherence.

### Sample size and power estimation

The PLUMM study is the largest clinical trial in pediatric LN, to the best of our knowledge, which is adequately powered. Sample size was determined from a combination of prevalence data and precedents in the literature [13,14,35–43]. A sample size of 45 subjects per group with proliferative LN is anticipated to provide a power of 80% for the primary aim of detecting a significant difference in the rate of PRR between the MMF_PK_ and MMF_BSA_ arms at the end of Part 1, at a 2-sided 5% significance level by a two-group Chi-square test, assuming the rate of PRR is 55% in MMF_BSA_ and 83% in MMF_PK_. The sample size of 90 will ensure 81% of power to detect a statistically significantly difference in the rate of CRR between the two study arms, assuming a smaller proportion of 14% and a larger proportion of 43%. Based on the above presented power analyses, we will plan to enroll 105 subjects, to allow for up to 14.3% attrition rate during Part 1 of the study.

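### The 105 is justified as though dropouts leave the analysis, but the non-responder rule keeps them in; the stated 80% power is therefore not derived from the planned analysis and could be about 71% at the plan's own attrition ceiling

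*Protocol article*

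**What the plan says.** All of this is in the protocol article.

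- **Sample size and power estimation**, primary outcome: "A sample size of 45 subjects per group with proliferative LN is anticipated to provide a power of 80" per cent. This refers to PRR when Part 1 ends, tested by chi-square with a two-sided alpha of 0.05. The rates behind it are given in these words: "assuming the rate of PRR is 55% in MMF_BSA_ and 83% in MMF_PK".
- **Same section**, complete renal response (CRR): "The sample size of 90 will ensure 81% of power", for 14% against 43%.
- **Same section**, enrolment: "we will plan to enroll 105 subjects, to allow for up to 14.3% attrition rate during Part 1 of the study".
- **Randomization**: "Eligible subjects enrolled in the study will be randomized (1:1) at baseline to receive either MMF_PK_ or MMF_BSA".
- **Statistical analysis**: the primary comparison uses a method for a binary outcome, "such as Chi-square test, Fisher’s exact test, or a Bayesian approach with non-informative Beta prior". Shortly after comes the rule for dropouts: "Subjects who discontinue the treatment due to any reason will be considered as being non-responders".

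The article does not say whether the assumed rates already count subjects who stop treatment as failures. It describes the trial as adequately powered both in the sample-size section and in the Discussion.

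**The concern.** Dividing an evaluable sample size by one minus the dropout rate is right when dropouts supply no outcome and are left out. Those who remain then respond at the assumed rates, and the target number is preserved.

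Non-responder imputation works differently. Nobody is left out, so the number analysed is 105 and not 90. Each discontinuation enters as a failure, so both rates shrink in proportion and the absolute difference shrinks with them. Extra subjects offset some of that loss but do not restore the effect size on which the 80% was computed.

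What is at stake is how a null primary result would be read. A reader would take it as coming from a trial with at least 80% power for the stated effect. At the attrition the plan says it allows for, that may not be so.

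**Working it through.** **Inputs.** 45 per group, two-sided 5%, chi-square test, PRR 55% and 83%, CRR 14% and 43%, 105 enrolled and attrition up to 14.3% (Sample size and power estimation); 1:1 allocation (Randomization), so 52.5 per arm on average; discontinuation counted as non-response (Statistical analysis).

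**Formula.** With n per arm, d = |p1 − p2| and p̄ the mean of the two rates,

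power = Φ[(d − 1.96·s0) / s1], where s0 = √(2p̄(1 − p̄)/n) and s1 = √((p1(1 − p1) + p2(1 − p2))/n).

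The continuity-corrected version replaces d by d − 1/n.

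**Step 1: the plan's own figures.** For PRR at n = 45: d = 0.28, s0 = 0.0975, s1 = 0.0929, so power = Φ(0.957) = 83.1%. With continuity correction it is 76.3%, and by exact enumeration of Fisher's test 77.7%. The stated 80% lies between these. For CRR at n = 45 the result is 87.5% uncorrected and 81.6% corrected, the latter close to the stated 81%.

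**Step 2: the 105.** 90/(1 − 0.143) = 105.02, and 15/105 = 14.3%. The figure reproduces, and it does so as the step that removes 15 subjects and keeps 90.

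**Step 3: the non-responder rule applied to 105.** Treat the assumed rates as on-treatment rates and let a fraction a of each arm discontinue. The analysed rates are 0.55(1 − a) and 0.83(1 − a). At a = 15/105 they are 0.55 × 6/7 = 47.1% and 0.83 × 6/7 = 71.1%, a difference of 24 points instead of 28. With n = 52.5, s0 = 0.0959 and s1 = 0.0930, so power = Φ(0.558) = 71.2%. Exact enumeration of the uncorrected test with 52 and 53 subjects also gives 71.2%.

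| Attrition, equal by arm | PRR rates analysed | PRR chi-square | PRR Fisher | PRR continuity-corrected | CRR chi-square |
|---|---|---|---|---|---|
| 0% | 55.0 / 83.0% | 88.5% | 87.2% | 83.6% | 92.0% |
| 5% | 52.3 / 78.9% | 82.8% | 81.4% | 76.8% | 90.0% |
| 10% | 49.5 / 74.7% | 76.6% | 75.1% | 69.8% | 87.6% |
| 14.3% | 47.1 / 71.1% | 71.2% | 68.9% | 63.8% | 85.3% |

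Chi-square power for PRR crosses 80% at a = 7.3%. The 0% row also gives the power if the assumed rates already count dropouts as failures.

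**Step 4: unequal attrition.** With 19% in one arm and 9.5% in the other (average 14.25%):

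- higher loss in the PK-guided arm: 0.55 × 0.905 = 49.8% against 0.83 × 0.81 = 67.2%, power 44%;
- higher loss in the BSA arm: 0.55 × 0.81 = 44.6% against 0.83 × 0.905 = 75.1%, power 90%.

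**The case against.** **A reader might infer that power simply is 71%.** The documents do not support that. The figure needs on-treatment rates, attrition that is the same thing as treatment discontinuation, the full 14.3%, and equal loss in both arms. The article states none of the first, second and fourth, and 14.3% is a ceiling rather than an expected rate. The rates are attributed to prevalence data and literature precedents, and the article does not say how those sources counted withdrawals. This objection stands, and it is why the result is given as a range.

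**Attrition and discontinuation may differ.** The sample-size section uses the first word and the non-responder rule the second. The Discussion says that patients who leave for other therapy are still monitored, while the Statistical analysis section says discontinued subjects supply no measures. The point is fair. Even so, the article shows no other rule for such subjects in the binary primary analysis.

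**Inverse propensity weighting might cover dropout.** That text follows the continuous exploratory endpoints and the Kaplan-Meier plots. Where it stands, it does not displace the non-responder rule for the primary outcome.

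**A reader might infer a fall from 80% to 71%.** That comparison mixes formulas. Like for like the fall is 83% to 71% by chi-square, or 76% to 64% with continuity correction.

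**A reader might also make much of the two stated powers not matching one test.** This is minor. The named chi-square test gives more than the stated figure for both outcomes at 45 per arm, so the stated figures are conservative before attrition.

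**A reader might infer that enrolment should drop to 90 if the rates already include dropouts.** That does not follow. The extra 15 would then add power and need only a different justification.

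**Conclusion.** The inconsistency stands on the text alone: the step from 90 to 105 assumes that dropouts are excluded, and the primary analysis includes them as failures. The stated 80% therefore does not describe the analysis that is planned.

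Its size depends on what 55% and 83% mean. If they are on-treatment rates, with attrition equal to treatment discontinuation and balanced by arm, chi-square power for PRR runs from about 83% at 5% attrition to 71% at the ceiling (69% by Fisher's test, 64% with continuity correction). The chance of missing the assumed effect at the ceiling is then about 29%, not 20%. If the rates already count dropouts as failures, power is about 88%. Unequal loss can move the result well to either side.

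CRR is little affected: about 85% by chi-square at 14.3% attrition, above the stated 81%. The finding is that the primary power is not established as written. It is not that the trial is shown to be underpowered.

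**What to change.** Keep enrolment at 105 and revise the sample-size section as follows.

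1. State whether 55%/83% and 14%/43% already count subjects who discontinue treatment as non-responders, and whether attrition there means treatment discontinuation.
2. Restate power for PRR and CRR on all randomised subjects under the non-responder rule, using one named test for both.
3. Give a short table over attrition from 0% to 14.3%, like the one above.
4. If the rates already include discontinuations, replace the attrition rationale with the power that 105 provides.

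The change is one of wording and needs no extra patients. The only downside is that, under the on-treatment reading, the stated primary power becomes less favourable. For information, 80% by chi-square at 47.1% against 71.1% would take 65 per arm (130 in all). That number matters only if the sponsor confirms that reading and wants 80% at the ceiling.
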